#### Framework for Reporting Adaptations and Modifications – Enhanced (FRAME) and Evidence-based Implementation Strategies (FRAME-IS)

FRAME consists of eight aspects including whether the intervention adaptation was planned or unplanned, the extent the adaptation is fidelity consistent and the intent or goal of the modification [30]. The FRAME-IS consists of four core elements to guide documentation: (1) describing the evidence-based practice, implementation strategy and adaptation; (2) what is adapted; (3) the nature of the adaptation; and (4) the rationale for the adaptation [31]. Delivery and adaptation of the Navicare intervention and implementation strategies will be guided by FRAME and FRAME-IS respectively across the study period and sites. This will assist in determining modifications to Navicare and implementation strategies that were associated with successful versus unsuccessful implementation as well as core implementation strategies [30, 31].

#### World Health Organisation ExpandNet framework (ExpandNet/WHO)

The validated ExpandNet/WHO framework consists of the elements of the intervention, user organisation(s), environment, resource team, and scaling-up strategy and is guided by the principles of systems thinking, a focus on sustainability, the need to determine scalability, and respect for gender, equity and human rights principles [32, 33]. The framework will be utilised in developing a scalability strategy with stakeholders during a roundtable workshop.

### Implementation study component methods

This study component will address aims 1 to 4.

#### Population

The inclusion criteria for service user or carer participants (over the age of 16 years) are, being a current or past user of Navicare in any of the site locations or broader mental health services in the region. Service providers and other participants will be included if they are a current or past service provider through Navicare or are connected with Navicare as a relevant stakeholder, including Care Navigators, community members, government agencies and policy makers. Roundtable stakeholder participants will include: experts in mental health across Australia (including those in regional mental health and recovery-based programs); at least two people with lived experience of mental ill-health; a Care Navigator from Navicare; and representatives from non-government and government mental health agencies, including policy makers.

#### Recruitment

Potential individual participants (e.g., service users, carers and service providers) will be contacted by a member of the study team or a study partner with an existing relationship to the provider or user, but not by the service providers of users (e.g., psychologists, social workers). Initial contact will be made in the form of an email, newsletter or flyer outlining the intent of the research and information on how to participate. Potential participants who are interested in taking part will be required to contact the research team if they would like to participate, following which information and consent forms will be sent to them. Potential participants who respond to a request to participate may be asked to complete screening questions as part of the process to ensure diverse representation in qualitative study activities (e.g., age, gender). Participants must provide written consent prior to engaging in community consultations, interviews, implementation diaries, the roundtable, and workshops. Non-English speaking potential participants and people with language impairments will be able to participate if they have a support person who is able to assist with translation and language assistance.

#### Data collection

The sampling approach for qualitative data collection will be convenience sampling initially, followed by purposeful sampling then theoretical sampling [34] with diverse representation sought as part of our recruitment strategy (Table 2). Routinely collected deidentified Navicare service-level data will be accessed, including sociodemographic data and telehealth usage. Sociodemographic data will also be collected from Navicare users and providers who consent to participate in interviews, focus groups and surveys.

**Table 2 Tab2:** Characteristics of stakeholder groups sought for diverse representation

Service users	Service and support providers
- Ages including young people 16 to 18 years and 18 to 24 years, older persons - Non-binary genders - Type of service user (e.g., local resident, Drive In Drive Out/ Fly In Fly Out worker) - Previous experience with Navicare (those with lived experience and no lived experience) - Socioeconomic circumstances (e.g., employed, not employed) - Diverse cultural and linguistic backgrounds - With and without lived experience of mental ill-health - Service users of Navicare and other services - Community members who have not accessed Navicare services but have lived experience of mental ill-health - Parents and carers of people with mental ill-health	- Representation from local government, Primary Health Network, community support organisations like local sporting organisations, telehealth providers, general practitioners and allied health professionals, educators, policy makers, Lifeline, alcohol and other drugs support workers, community housing - Local businesses (mining and industry) - Diverse cultural and linguistic backgrounds

#### Co-primary outcome

Our novel co-primary outcome measure of sustained access to Navicare was identified in our initial intervention co-design work with communities as being of great importance [9]. This outcome will be evaluated using the total number of new eligible persons with or at risk of mental ill-health or their carers who seek assistance from or through Navicare each month either directly or by provider referral. These data will be obtained from routinely collected Navicare service data. Access will be measured monthly across the study, comparing implementation (12-months) and sustainment (12-months) phases across all new sites, with commencement defined according to when the first client is seen physically at each new local site (see Fig. 2). We consider this outcome to bear similarity to Proctor’s outcome of equitable access, with access hypothesised to combine the outcomes of penetration, sustainability and fidelity [28].

#### Implementation outcomes and adaptation

Mixed methods data will contribute to the outcomes of acceptability, adoption, fidelity, sustainability, cost of implementation, implementation, and adaptation. Qualitative data will contribute to feasibility, appropriateness and scaling-up. The following outcome measures and approaches will be used, with measurement timepoints and further details outlined in Tables 1 and 3. Outcome measures to be used include the *Navigation Satisfaction Tool (NAVSAT)* [35], *Program Sustainability Assessment Tool (PSAT)* [36] and a *fidelity-adaptation tool* to be developed as part of the study. The tool will document core non-adaptable and modifiable intervention components and the extent to which Navicare intervention activities are delivered as planned or adapted to meet local community needs, and explore reasons underpinning adaptations (detailed in Table 3).

**Table 3 Tab3:** Protocol outcome measures

Outcome measure	Outcome	Time of data collection and people completing	Description, scaling and content	Psychometric and other properties
Navigation Satisfaction Tool [34]	Acceptability in terms of satisfaction with care navigation and referral services used by service users	Navicare service users will complete up to 6-months after intake to Navicare or 3-months after last contact with Navicare	22-items rated on a likert scale from 1 (extremely dissatisfied, extremely unhelpful, or extremely small degree) to 7 (extremely satisfied, extremely helpful, or extremely large degree). Topics covered include the navigator’s ability to listen and understand service user concerns, the mental health system, information about potential treatment options, intake procedures, navigator’s helpfulness, likelihood of recommending the service, and overall satisfaction with the service, as well as levels of perceived effectiveness and satisfaction with aspects of the referred service [34]	Acceptable reliability, face validity, and predictive validity for service users of care navigation services [34]
Program Sustainability Assessment Tool [35]	Sustainability at the program level	Navigators and the research implementation team will complete at the end of one year of implementation at each site	40-items rated on a Likert scale from 1 (‘to little or no extent’) to 7 (‘to a very great extent’). Eight domains are environmental support, financial stability, partnerships, strategic planning, communications, program adaptation, program evaluation, and organisational capacity	Good fit of the data with the 8 domains using confirmatory factor analysis and acceptable internal consistency when used in chronic disease programs [35]
Study specific fidelity-adaptation tool	Fidelity and adaptation	Research implementation team will complete throughout the study. Member checking by the original co-developers of the Navicare model and implementation strategies	Items specific to the study will be developed based on FRAME, FRAME-IS, elements of adaptation [36], and the proportion and duration of activities in each phase similar to the Stages of Implementation Completion measure [37]. Data from multiple data sources will be mapped to the tool items (e.g., from semi-structured interviews, community consultations, workshops, observations at forums or site visits, implementation diaries and documents referred to in data collection activities). Member checking will be conducted against originally developed core intervention components and implementation strategies [36, 38]	Not applicable

*Abbreviations*: *FRAME* Framework for Reporting Adaptations and Modifications – Enhanced (FRAME), *FRAME-IS* Framework for Reporting Adaptations and Modifications – Enhanced Evidence-based Implementation Strategies (FRAME-IS)

*Implementation diaries* will be used to collect information on everyday work of Navicare to report on the process of care navigation as well as being a tool to capture resource use, and barriers and facilitators to implementation. Implementation diaries will be completed by Care Navigators throughout the implementation and sustainment phases to allow an in-depth understanding of project implementation by capturing project evolution and real-time insights while reducing self-reporting bias [39, 40]. The structure of the diaries will be based on the EPIS framework constructs as well as implementation outcomes relevant to the study. Implementation diaries will be completed monthly in the implementation and sustainment period at the new study sites, hosted in Redcap, an electronic data capture tool [41].

*Context assessment and evaluation of contextual factors* (for example, barriers and facilitators, mechanisms) will be conducted using a hybrid inductive-deductive approach. Constructivist methodology [42, 43] will underpin the inductive approach, and EPIS study phases will inform the deductive approach to capture how these factors influence the findings. Using constructivist methodology has been reported to promote a multi-layered approach and can assist in building a holistic understanding of context as dynamic across the study rather than static, capturing interactions within context and maximising uptake and sustainability when used to inform subsequent phases of implementation [42]. Context and interactions between context, intervention, and implementation will be used to prospectively inform subsequent study phases and will be analysed separately from implementation processes [42]. Data sources will include semi-structured interviews, community consultations, and workshops with service users, carers, and service providers at all sites; and observations at forums or site visits. Field notes and memos will be made in relation to all data sources.

*Scaling up* nationally will be prepared for using a national roundtable forum in the final year of the study, with subsequent email or virtual feedback from participants to summarise themes, recommendations and evidence-based practice gaps for sustainability and national scaling of Navicare [32]. ExpandNet resources will be used including the ExpandNet/WHO framework for scaling up [32, 44]. A scalability strategy will be co-developed with stakeholders using the ExpandNet/WHO Nine Steps for Developing a Scalability Strategy [32] if evidence collected from the four study sites supports success aligned with the study aims. The actions and findings throughout the preceding four EPIS phases will directly support this process and provide evidence of the scalability of Navicare nationally.

#### Data analysis

The co-primary implementation outcome of sustained access will be analysed quantitively using a regression model. A hybrid mixed methods approach integrating inductive and deductive qualitative analyses will be used for qualitative data. Inductive analyses will be informed by constructivist grounded theory [45] and deductive analyses will be conducted using framework analysis. These analyses will involve constant comparison (systematic comparison across participants) throughout the study and developing and charting data into a working framework [46]. The working framework will be based on the EPIS, study sites, and ExpandNet/WHO frameworks, the fidelity-adaptation tool [47], or other factors identified from the inductive analysis. Themes will be summarised to generate recommendations for scaling up Navicare or alternate mental health access and support programs, and to highlight evidence-based practice gaps.

Quantitative data analysed descriptively or using regression models will be combined with qualitative data to report on the implementation outcomes, context and contextual factors influencing implementation, and outcomes related to the process of applying EPIS (for example, variability in the timing of the exploration and preparation phases across sites prior to new site implementation) where relevant. As part of this mixed methods approach, qualitative and quantitative data will be used for sampling, triangulation, elaboration, expansion and development of the data [48]. The latter will involve using the findings to inform the development of implementation strategies. The process of combining the qualitative and quantitative data is expected to involve merging, connecting and embedding both types of data [49]. Trustworthiness of qualitative and mixed methods analyses will be maintained using field notes, reflexive journaling, memoing, and member checking of data [43, 45, 49]. Visualisation techniques (for example, causal loop diagrams and social network analysis) will be used to report on and provide feedback during the study on the study outcomes (for example, service access) and mechanisms of action of the implementation [50–52].

Cost of implementation will be evaluated across the study sites as well as for each EPIS phase and will include engagement of a local working group during preparation and implementation. Regression models will be used to explore the association between quantitative outcomes (for example, fidelity using the fidelity-adaptation tool with the implementation outcome of sustained access).

#### Implementation strategies

It is expected that multiple implementation strategies will be selected, implemented, and tailored to each site. These strategies are likely to include community and stakeholder engagement and access to local infrastructure. The *Expert Recommendations for Implementing Change (ERIC)* will be used to describe strategies, with FRAME-IS used to guide documentation on how strategies were adapted in the broader context of rural and remote Australia [31, 53]. Other potential strategies not captured by ERIC will be identified and described using the hybrid inductive and deductive data analysis approach (including the use of EPIS to identify barriers and facilitators).

### Effectiveness study component methods

This study component will address aim 5.

#### Population

People with mental health related hospital data from public hospitals in the Greater Whitsunday Region and major regional hospitals situated just outside the Region will be included.

#### Data collection

Local and district hospital level data from the Queensland Hospital Admitted Patient Data Collection (QHAPDC) and Queensland Hospital Emergency Department Data Collection (QHEDC) will be obtained for new sites for the 24-months prior to commencement, during the implementation period of 12-months, and for 12-months in the post-implementation (sustainment) period. The longer length of pre-implementation data will be used to account for seasonal patterns in this control period. For the existing site, QHAPDC and QHEDC data will be collected for 12-months pre-implementation to avoid, as much as possible, the major disruptions due to the COVID-19 pandemic in the first half of 2020, and for the implementation period will be collected from October 2021 when the first client accessed the service. Post-implementation data will be collected from July 2025 at the existing site.

#### Co-primary and secondary outcomes

Outcomes will include time in an emergency department for mental ill-health (co-primary outcome), and mental health crisis-related Emergency Department attendances and admitted overnight hospitalisations for mental ill-health (secondary outcomes).

#### Data analysis

A pre-post comparison analysis will be used to examine if Navicare has a greater effect than any underlying secular trend. This will be achieved by fitting a generalised linear mixed model, to model the monthly rates of time in the emergency department (using a Gamma or normal distribution depending on the data), mental health emergency department presentations (using a Poisson distribution), and admitted overnight hospitalisations (using a Poisson distribution) [54]. Random intercepts will account for the non-independence of data from the same facilities. For sustained service access (co-primary outcome) and adoption, the trend before and after formal support for Navicare ends will be modelled (implementation to sustainment periods, Hypothesis 1). Residuals of the models used will be checked to assess the model’s validity, with histograms to check for bimodality and outliers, and with autocorrelation over time assessed with the Durbin Watson test, and adjustments for underlying trends and seasonality.

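### Poisson is fixed for the two secondary hospital counts with only facility intercepts for dependence, so before-after intervals are too narrow if overdispersion or residual autocorrelation is present

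*Protocol article*

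**What the plan says.** All of this stands in the protocol article, under Effectiveness study component methods.

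- **Counts.** Data analysis specifies a generalised linear mixed model for monthly rates, with "mental health emergency department presentations (using a Poisson distribution), and admitted overnight hospitalisations (using a Poisson distribution". No alternative distribution is named.
- **Emergency department time.** The same sentence leaves this distribution open, "using a Gamma or normal distribution depending on the data".
- **Dependence.** "Random intercepts will account for the non-independence of data from the same facilities". No other random effect or correlation term is named.
- **Checks.** "Residuals of the models used will be checked to assess the model’s validity, with histograms to check for bimodality and outliers", followed by "autocorrelation over time assessed with the Durbin Watson test, and adjustments for underlying trends and seasonality". The article does not say what follows if autocorrelation is found.
- **Status.** Co-primary and secondary outcomes lists the counts as "mental health crisis-related Emergency Department attendances and admitted overnight hospitalisations for mental ill-health (secondary outcomes". Time in the emergency department is the co-primary.
- **Series length, new sites.** Data collection gives "24-months prior to commencement, during the implementation period of 12-months, and for 12-months in the post-implementation (sustainment) period", which is 24 + 12 + 12 = 48 months.

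**The concern.** Each facility contributes months before and after the service starts, and the phase effect compares those months within the facility. The facility intercept cancels out of that comparison. Its precision depends on how much monthly counts scatter around the fitted trend and season, and on whether neighbouring months move together. The stated model fixes the first at the Poisson value and sets the second to zero.

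Both assumptions are doubtful here. People with mental ill-health re-attend and are re-admitted, so events cluster within persons and monthly totals tend to vary more than Poisson allows. Local conditions such as staffing or service closures last longer than a month.

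The planned checks offer little protection. A residual histogram for bimodality and outliers does not measure dispersion. Durbin-Watson is a lag-1 test built for a single linear-regression series, and the article does not say how it would be applied across facilities in a generalised mixed model or what would change if it rejected.

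What is at stake is a false claim that Navicare changed hospital use. The Discussion acknowledges that there is no control group, so the evidence rests on the precision of this time contrast.

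**Working it through.** The article gives no rate, power or interval width for the hospital counts, so there is no stated figure to reproduce. The dispersion, correlation and mean counts below are assumptions.

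**Dispersion, analytic.** If the variance is φ times the mean, the true standard error is √φ times the Poisson one. The nominal 5% two-sided test then has error 2 × (1 − Φ(1.96/√φ)).

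| Assumed φ | √φ (width ratio) | 1.96/√φ | Error rate | Coverage |
|---|---|---|---|---|
| 1 | 1.00 | 1.96 | 5.0% | 95.0% |
| 1.5 | 1.22 | 1.60 | 11.0% | 89.1% |
| 2 | 1.41 | 1.39 | 16.6% | 83.4% |
| 3 | 1.73 | 1.13 | 25.8% | 74.2% |

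**Counts, simulated with trend and season in the model.** Four facilities × 48 months, staggered starts, Poisson regression with facility intercepts (fixed, standing in for random), linear trend, annual sine and cosine, post-start indicator, true effect zero, 600 runs per setting. The extra variation has squared coefficient of variation (CV²) 0.05, so the implied φ is 1 + 10 × 0.05 = 1.5 at a mean of 10 per facility-month and 1 + 40 × 0.05 = 3 at a mean of 40.

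| Data | Coverage, mean 10 | Coverage, mean 40 |
|---|---|---|
| Pure Poisson, independent months | 96.2% | 95.0% |
| Extra variation, CV² 0.05 | 87.5% | 73.2% |
| Same, plus lag-1 correlation 0.4 | 80.7% | 59.0% |

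- The first row shows that the model is sound when its assumptions hold.
- The second row is close to the analytic 89.1% and 74.2%. Adjusting for trend and season does not remove this kind of variation.
- In the third row, Pearson dispersion was 1.49 and 2.96, so a dispersion correction would widen intervals by √1.49 = 1.22 and √2.96 = 1.72. The estimate's actual standard deviation was 1.49 and 2.30 times the average model standard error. Correcting dispersion alone leaves a shortfall when months are correlated.

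**Emergency department time, simulated.** Normal model, three facilities × 48 months, staggered starts, facility effects, trend and annual terms, no true effect, 4,000 runs. The error rate was about 5% with independent months, about 13 to 14% at lag-1 correlation 0.3, and about 22% at 0.5. A free residual variance corrects the scale but not the correlation.

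**The case against.** The strongest reply is that this is a condensed article. It commits to checking residuals for model validity and to adjusting for trend and seasonality, it collects 24 baseline months with seasonality in mind, and it nowhere says Poisson would be kept if a check failed. A fallback may stand in an analysis plan that is not shown.

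Part of this stands. The adjustment removes some extra variance and autocorrelation, and an unstated fallback alone would be no finding. But the article does more than omit one. It fixes Poisson for the counts while leaving the distribution of emergency department time open, and it presents facility intercepts as the answer to non-independence, which they are not for a within-facility contrast.

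Four stronger readings are not supported:

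- **That intervals will be too narrow in any case.** Simulated coverage was 95 to 96% with conditionally Poisson, independent counts, and the article gives no dispersion or autocorrelation value.
- **That the Poisson choice reaches a co-primary.** Both Poisson outcomes are secondary. Sustained access is described only as a regression model, with no distribution named. Only the autocorrelation point extends to emergency department time.
- **That the cost-saving intervals inherit the same standard errors.** The economic Data analysis section uses non-parametric bootstrapping for uncertainty.
- **That Durbin-Watson would probably miss the correlation.** Its power depends on how the facility series are combined, which is not stated. The firm point is that no action follows from it.

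**Conclusion.** The point holds conditionally. As written, the model for the two secondary counts gives correct intervals only if counts are conditionally Poisson and independent between months after trend and season are removed. Under assumed dispersion of 1.5, 2 or 3, the nominal 5% two-sided test has about 11%, 17% or 26% false positives, and positive serial correlation makes this worse. The co-primary model for emergency department time is exposed to residual autocorrelation but not to the Poisson restriction. Repeat attendance makes overdispersion plausible, but the documents do not establish it, so the actual shortfall cannot be sized from them. The plan should change because a safer model costs little.

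**What to change.** In Data analysis of the effectiveness component:

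1. Replace Poisson with negative binomial (or quasi-Poisson) for emergency department presentations and overnight admissions.
2. For all hospital models, including emergency department time, pre-specify a within-facility month-level correlation term such as AR(1), or autocorrelation-robust standard errors. Do not make this depend on a preliminary test.
3. Check residual autocorrelation separately for each facility, in place of relying on Durbin-Watson.

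A facility-by-phase random effect is not asked for as a requirement, since its variance would be poorly estimated with so few facilities.

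The change is to analysis wording and needs no new data. Intervals become about 1.2 to 1.7 times as wide at dispersion 1.5 to 3, and wider again if months are also correlated. Little precision is lost if the counts turn out to be close to Poisson and independent.
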